### Intervention

Intervention consists of:-5-minute videos, on various stroke-related topics/themes delivered at the time of enrollment into the study, before discharge from the hospital, at first and third month follow-up post dischargeSession 1 will be delivered at the time of enrollment into the study and will cover themes on information for caregivers including recognition of stroke, and different skills will be taught to the caregivers including swallowing exercises, different rehabilitation exercises and naso-gastric tube feedingSession 2 will be delivered at the time of discharge from the hospital and will include videos on emergency preparedness – cardiopulmonary resuscitation, seizures, heart attack, hypoglycemia and recurrent strokeSession 3 will be delivered at first month follow-up post discharge and will include videos on frequently used medications by stroke survivors, such as anticoagulant, antihypertensive and lipid-lowering drugsSession 4 will be delivered at third month follow-up post discharge and will include videos on secondary stroke prevention (recurrent attack) – exercise, physical activity, recognition of depression, diet modification and accurate measurement of blood pressure and blood sugarPlease refer to Additional file 4 (Video Thematic Intervention Chart) which demonstrates the core messages that will be delivered in the videosDiscussion and question and answers after viewing each set of videos to ensure that the core message has been understood and there are no lacunae in understanding the message imparted by the videos, which may be re-wound and re-run for those who could not understand a particular messageMovies4Stroke Application Installation in a memory card – a memory card containing the movies application will be installed in the participants’ cell phones in the intervention group to ensure that the videos can be replayed at home to refresh the memory of various details which may not have been captured in the mandatory viewing session that captures the usage data

### Compliance during the administration of intervention

The study officer, after receiving randomization to the intervention group will perform the following functions:Ensure that there is space and time for both caregiver and stroke survivor to feasibly watch the videos and that both are receptiveEnsure that there is no contamination by delivering the video in a non-public area – participant’s room if private or semi-private, counseling room if a general ward patientEnsure that the sound quality is at a level that is clear to both stroke survivor and caregiver and that both are receptiveEnsure that the caregiver sees all the videos in the tablet at least once as administered by the unblinded study officerCheck if the videos can be replayed on the dyad’s home Android systems and that there are no technical issues

### Video translation and adaptation

The science in the videos is based on class I A evidence [18, 19]. However, the language of the instructions and the setting will be tailored according to culturally accepted norms [20]. Specifically, we want local resonance and acceptability [21]. Videos prior to being launched in the field will be shown to laypersons, stroke survivors and stroke caregivers to obtain feedback. Since this is a digital media, editing the same is feasible. Those who will assess the movie content in the pre-testing phase of the intervention will not be recruited in this implementation study.

The 5-minute idea is to hold attention, offer repeatability and engender self-efficacy [20, 22]. There should be sense of empowerment with manageable information. This is very important for cognitive, literacy and numeracy impaired populations [23]. For future scalability, digital media that last for 8–10 minutes can take excessive space and time downloading which can lead to user frustration and failure [24, 25]. Since these videos will be a resource, they should tend to be user friendly across platforms and systems, and time compression would achieve that goal. A similar concept has also been utilized in medical education internationally [26].

### Measuring adherence to video intervention

To ensure adherence to intervention in the video group, at least one viewing will be delivered in the hospital or the CTU through active involvement of stroke survivors and their caregivers. In order to ensure that each important learning point is made clear in the first session, the key pre-test and post-test knowledge questions, which will be embedded in the movie application software for each set of movies, will form a template for testing and discussion. Throughout the videos, both stroke survivors and their caregivers will be encouraged to ask questions and clear their queries with the respective team members, and questions and answers accompany each video to provide a platform for discussion and comprehension. Since learning is enhanced by repetition, we will enable repeat viewing with a phone card memory application that contains the relevant videos [27]. Thus, those who are too stressed to learn in the first place, or who are older adult learners, will have the ability to review the videos in addition to the mandatory session. The Movies4Stroke Application Software (Refer to Fig. 3) will have the ability to monitor video usage and views by the user. This will help us in calculating the ‘sticky time’ (time spent using and interacting with the movie application software), the rationale being that we will be able to track actual usage of our intervention in the video arm in real time.

**Fig. 3 Fig3:**
[figure not shown]
User interface snapshots of the movie software

### Standard of care for stroke survivors (control group)

Stroke survivors will be given instructions before discharge regarding diet, need for rehabilitation, possible complications, and medication use and information booklets will also be handed out. The information will be imparted by a multidisciplinary team consisting of a neuro-physician, a stroke nurse, a dietitian and a physiotherapist. There will also be verbal instructions given to the stroke survivors and their caregivers. On the day of discharge, or 24 hours prior to discharge, a discharge coordinator will give the details about the skills learnt and will ensure that the medical, social, and rehabilitation requirements are in place prior to leaving hospital. All acute stroke survivors will be given follow-up appointments at the clinic. A detailed written discharge summary will be given out to the caregiver detailing all aspects of care, follow-up, medications, test results and serious alerts. This standard of care will be followed for all participants including those who receive video-based intervention.

### Operational plan

#### Pre-field activities

##### Hiring and training of staff

Four experienced research associates will be recruited for a total duration of 12 months. One research supervisor will be recruited full-time for a total duration of 15 months. The research supervisor should at least possess an MBBS degree with relevant experience in clinical neurology. All the members in the team including the research supervisor will be given formal training in interviewing (data collection) for at least 2 weeks.

Research training will emphasize on the following areas:Introduction of the Study Project and the concerned team membersAdministration of the questionnaire and its completeness including the quality control procedures and compliance during the administration of the interventionContact information and follow-up proceduresEmphasis on communication skills and how the data collectors should communicate with the study participants and their caregiversProcedure pertaining to informed consentIntroduction to the video intervention and technical aspects of the software

### Pre-testing of the questionnaire

Pre-testing will be done on 20 % of the total sample size, that is 60 participant dyads, and those participants will be excluded from the final analysis. Questions that will require some changes due to phrasing and improper translation will be amended after pre-testing.

### Instructions for follow-up

Each stroke survivor caregiver dyad will be required to follow up at 1, 3, 6, 9 and 12 months post discharge in the neurology clinic for outcome ascertainment. Stroke survivors and their caregivers will be given a handout which will have instructions and basic information about their follow-up visits. Follow-up visit explanations will be given verbally to caregivers together with emphasizing the importance of their patient’s follow-up visit. They will be asked to contact the study team through our Stroke Helpline for any queries that arise in the interim period.

### Follow-up visits in the neurology clinic

Follow-up visits at 1, 3, 6, 9 and 12 months will be organized in the neurology outpatient clinic to assess outcome. In order to maximize our follow-up, participants will be sent short messaging service (SMS) reminders through our Stroke Helpline a day prior to the visit and transport will be arranged to facilitate the visit. If a stroke survivor along with their caregiver is not able to report for follow-up on the exact date, a grace period of ±14 days will be permitted to ensure capturing maximum follow-up. Those participant dyads that cannot appear for the follow-up in person will be contacted via phone or through establishing a follow-up visit appointment in synchrony with other clinical visits, physiotherapy sessions and laboratory investigations.

### Data management

#### Data management plan

A data entry officer will work in conjunction with the principal investigator (PI). The data entry officer will be given a formal training session on how to read the filled data forms and then enter it in the database. A codebook that contains specific number codes for each item of the questionnaire used in the data collection forms will be introduced to the data entry officer. The PI will request the data entry officer to enter the data for the five study participants in front of the PI so that any mistakes or discrepancies can be immediately rectified. A similar quality cross check will be performed during the double data entry process.

### Data editing

Data editing will ensure a complete data file for each participant. This will be done to check for any missing, incomplete or incorrect information provided at the time of interview by a stroke survivor or their caregiver. The data collectors will edit the filled questionnaire on a daily basis. Editing will be performed in two stages in order to avoid missing or inappropriate information. The field editing will be done by interviewers, just after the data collection process so that missing information can be obtained and any inappropriate information can be corrected. In case of missing or inappropriate information, the PI will contact the participant on their cell/home phone number for correction. Any missing information or discrepancies will be clarified immediately; every effort will be made to complete the information. The data will be double checked by a research supervisor and the PI on a weekly basis.

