## Methods

### Study design

This will be a randomized controlled, outcome assessor blinded, parallel group, single center superiority trial in which participants with first ever stroke (both ischemic and hemorrhagic) will be randomized within 48 hours of their stroke to either the video-based education intervention group or the control group [13]. The video-based education intervention group will have health education delivered through short videos which will be shown to the participants and their caregivers at the time of admission, before discharge, and follow-up at first and third month post discharge. The control group will have standard care including pre-discharge education and counseling according to defined protocol. All participants enrolled in this video education intervention group and control group will be followed for 12 months post discharge for assessment of end-points (Refer to Fig. 1).

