### Identification and enrollment of the study participants

Data collectors will screen the participants coming to AKUH Stroke Unit, Neurology ward, Karachi. Data collectors will fill out the eligibility form and, if the participants are found eligible for the study, they will be officially invited to participate in the trial. Informed consent will be obtained from those participants who voluntarily wish to be in our study. The study participants and their caregivers will be thoroughly counseled about the nature of the study and required follow-up. It will also be explained to study participants that the selection in the study group is random. Stroke survivors will then undergo a detailed interview regarding the socio-demographic, clinical and functional assessment at baseline. Then, the participants will undergo randomization to either the intervention group or standard care group. After allocation assignment, the research supervisor will thoroughly explain the details of the software program and its installation and then proceed with the delivery of the first set of 5- minute videos. Any questions pertaining to the use and the comprehension of the videos and software will be answered. Videos will be shown at the time of enrollment into the study, at discharge from the hospital, and follow-up at first and third months post discharge and a memory card containing the Stroke4Movie Application will be installed and programmed to deliver scheduled videos on the participant’s Android phone. In case of the participant being allocated to the usual care group they will be informed about the details regarding discharge and the follow-up appointments at the clinic (Refer to Fig. 2) (see Additional files 1, 2 and 3).

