### Secondary study outcomes

Change in knowledge of caregivers concerning stroke risk factors, stroke rehabilitation and medications (a knowledge questionnaire will be administered at 1, 3, 6, 9 and 12 months post discharge and change in score will be ascertained)Readmission to hospital with any of the stroke-related complications – urinary tract infection, pneumonia, and deep venous thrombosis (this information will be elicited at the follow-up time, based on recall. All participants will be asked to bring documents related to any hospital admissions in the period following discharge)Stroke-related mortality will be assessed through a Verbal Autopsy Scale adopted from the WHO [15]Change in functional outcome (severity and disability after stroke) from baseline among stroke survivors will be assessed through validated tools (NIHSS, Barthel Index and mRS) [16]Level of satisfaction with the intervention and acceptability of mHealth innovation such as videos on selected topics among stroke survivors and caregiver dyads to improve clinical outcomes. This will be done on a self-designed tool which ascertains the constructive and unpleasant attributes of using this mHealth technology (please refer to Form C, Data Collection Form for Stroke Survivors– see Additional file 1). This self-designed tool will be administered by a research supervisor who will be unblinded to the randomization group. This tool has design attributes based on Rogers’ Diffusion of Innovation Theory for ease, adoption, repeatability, and adaptability [17].

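### The weekly check of collected data is assigned to the sole research supervisor, who knows the allocation, so self-reported outcomes lose their masking after blinded collection

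*Protocol article*

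**What the plan says.** Under Study design, the protocol article describes a "randomized controlled, outcome assessor blinded, parallel group, single center superiority trial".

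Four other sections concern the research supervisor:

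- **Hiring and training of staff:** "One research supervisor will be recruited full-time for a total duration of 15 months".
- **Identification and enrollment of the study participants:** the supervisor's task with the videos after allocation is stated thus: "the research supervisor will thoroughly explain the details of the software program and its installation and then proceed with the delivery of the first set".
- **Secondary study outcomes:** the satisfaction and acceptability tool is "administered by a research supervisor who will be unblinded to the randomization group".
- **Data editing:** "The data will be double checked by a research supervisor and the PI on a weekly basis".

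Data editing also states the purpose of the exercise, in a sentence that ends by naming the caregiver: "This will be done to check for any missing, incomplete or incorrect information provided at the time of interview by a stroke survivor or their". Interviewers edit first, directly after collection. For what remains, "In case of missing or inappropriate information, the PI will contact the participant on their cell/home phone number for correction".

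Outcome assessment places medication adherence, hospitalizations since discharge and knowledge in the questionnaire filled out at each visit. The same section forbids assessors to look at the participant's phone or to ask about the videos. It has 30 % of participants asked whether that rule was kept, and it removes from the final analysis any participant whose assessor was unblinded.

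**The concern.** Blinded assessment protects an outcome only if the recorded answer stays out of reach of people who know the arm until it is final. Here, once a blinded assessor has filled out the questionnaire, it is reviewed every week by someone who knows the allocation and has a part in delivering the intervention. The review is described in terms of incorrect and inappropriate answers as well as blanks, so it calls for judgement. Whether a self-reported adherence answer looks wrong is the kind of judgement that knowledge of the arm can influence, even in good faith. If more queries are raised in one arm, more answers are reconsidered in that arm.

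Adherence is one of the two primary endpoints and rests on self-report. Caregiver knowledge and recalled readmission are secondary outcomes collected in the same way. The protocol treats loss of blinding at the assessor as serious enough to exclude a participant, so an unmasked step immediately afterwards does not fit its own standard.

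**Working it through.** No arithmetic applies. The question is whether the sections, read together, put an unmasked person in contact with outcome data.

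1. **Is it one person?** Secondary study outcomes and Data editing both use the indefinite article for the supervisor. Hiring and training of staff recruits exactly one. Both passages therefore describe the same post-holder.

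2. **Does that person know the allocation?** Yes. Secondary study outcomes says so outright. The enrollment section is consistent with it, since nobody can give the first video set to intervention participants without knowing who they are.

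3. **Does the weekly check reach outcome data?** The check is of the collected data, within a section whose stated object is information given at interview. Outcome assessment puts adherence, hospitalizations and knowledge in that questionnaire. These outcomes are therefore inside the check as described. HbA1c and LDL come from blood samples, and blood pressure is measured at the visit. None of these is interview information, so they are much less exposed.

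4. **Who can change an answer?** The section names two routes: interviewers correct just after collection, and the PI phones the participant. It does not say that the supervisor alters values or makes calls. The supervisor's possible influence is indirect: the check can identify an answer as needing clarification, and the PI can then act on it. That is an inference from the sequence of tasks, not a statement in the text.

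5. **Is the PI blinded?** The document does not say. The person who recontacts participants may or may not know the arm.

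6. **Is there a safeguard at this step?** The rules under Outcome assessment (no viewing of phones, no question about videos, the 30 % cross check, removal after unblinding) are all directed at assessors. Nothing in the document limits the supervisor's check to non-outcome fields or removes the arm from what the supervisor sees. Removing an arm label would in any case help little with a person who has met the intervention participants.

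The sections thus give an unmasked person a weekly review of self-reported outcomes, with an indirect route to queries and no stated protection.

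**The case against.** The strongest reply is that the design claim concerns the assessor, and the assessor remains blinded. Assessment happens at the visit under explicit restrictions, and a later look at completed forms does not unblind anyone who filled them out. This stands. A reader might infer that the weekly check contradicts or defeats assessor blinding; the document does not support that. The gap arises after collection.

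A second reply is that the supervisor has no stated power to query or amend. This also stands. A reader might infer that the supervisor corrects adherence answers or calls participants back, but the section gives those tasks to the interviewers and the PI.

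A third is that the supervisor's part in the intervention is easily overstated. The enrollment section assigns this person the explanation of the software and its installation, and the first set of videos; it does not say who installs the memory card. Compliance during the administration of intervention names an unblinded study officer for the viewing, without saying whether that is the same person. This is correct, but it does not matter for the conclusion, because the supervisor's unblinded status is stated directly.

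A fourth is that a journal article leaves data-management detail to the full protocol or to operating procedures. That would excuse silence. It does not cover this case, because the article actively assigns the check to a role that it elsewhere declares unblinded.

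**Conclusion.** The point holds as a weakness in protecting self-reported outcomes after blinded collection. The sole research supervisor, who is unblinded, shares the weekly check of interview data with a PI of unstated blinding status, and no safeguard comparable to the one for assessors applies. Adherence, caregiver knowledge and readmission are exposed; laboratory values and blood pressure much less so.

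The conclusion rests on two readings: that the indefinite wording refers to the one supervisor recruited, and that the weekly check covers the outcome questionnaires, as the section's stated purpose implies. That queries could be raised unequally between arms is a possibility, not something the protocol provides for.

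No size can be given. A reader might be tempted to compute an inflated error rate from 150 per arm and the 0.350 control proportion under Sample size calculation. That proportion belongs to control of blood pressure, cholesterol and blood sugar, not to adherence, and both the number and the direction of changed answers would have to be invented.

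This should be corrected because it touches a central design claim and is easy to close. It does not invalidate the trial.

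**What to change.** Revise Data editing as follows:

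- Limit the unblinded supervisor's check to intervention-delivery, usage and satisfaction forms.
- Assign the weekly check of outcome questionnaires to staff already planned who do not know the allocation, with the arm identifier removed. One of the four research associates or one of the two data entry operators could do this. The article does not say that either group is blinded, so the text must state that the chosen person is kept so.
- Assign any call-back that could change an outcome answer to blinded staff as well. State the PI's blinding status, and let the PI make such calls only if blinded.
- Log every change to an outcome value with date, reason and the role of the person making it.

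The cost is a few sentences in the protocol or operating procedure and the reassignment of an existing weekly task, with no new post. The small downside is that the checker cannot draw on knowledge of the case when resolving a query.
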